### Outcomes

The outcomes are self-report inventories, clinical assessments and register-based data that will be used to detect potential changes in a variety of outcomes.

### Primary outcome

The primary outcome is change in the personal recovery experienced from pre-treatment to post-treatment and follow up measured by the Questionnaire about Process of Recovery (QPR) [49]. The scale was originally developed in collaboration with service users, and has been widely used to capture peoples’ accounts of recovery from severe mental illness. Participants are asked about aspects of recovery that are meaningful and relevant to a broad range of patients. In line with the definition of personal recovery, the items capture “a process of changing one’s attitudes, values, feelings, goals, skills, and/or roles. It is a way of living satisfying, hopeful and countering life even with limitations caused by illness” [69]. The 15-item version has been recommended for use both in routine clinical work and in research, and it is scored on a 5-point scale from 0 = disagree strongly to 4 = agree strongly). The psychometric properties in terms of internal consistency, test re-test reliability and convergent validity were found to be high [42].

### Secondary outcomes

Perceived functional impairment associated with mental health problems is assessed using The Work and Social Adjustment Scale (WSAS [48];), a self-report questionnaire. The scale has five items covering the following dimensions; influence on work, home management, social leisure activities, private leisure activities and relationships with others. The items are scored from 0 to 8, with a total score from minimum 0 to maximum 40, with lower scores indicating better adjustment. The scale has been found to have high internal reliability and sensitivity to treatment effects and has been recognized as an additional outcome measure alongside traditional symptom scales [72]. The scale was recently found to be a reliable, unidimensional and gender-invariant measure, sensitive to change among Norwegian outpatients with interpersonal problems [53].

Symptoms of PTSD and of complex PTSD (CPTSD), as presented in ICD-11, are measured with the newly developed self-report questionnaire the International Trauma Questionnaire (ITQ [15];). The ITQ contains 12 items: 6 covering the three clusters of PTSD (re-experiencing of the trauma in the here and now, avoidance of traumatic reminders and persistent sense of current threat that is manifested by arousal and hypervigilance), and 6 reflecting the three clusters of disturbances in self-organization (DSO) in CPTSD (affective dysregulation, negative self-concept and disturbances in relationships). Items are scored on a Likert scale from 0 (not at all) to 4 (extremely) to indicate how much the participant has been bothered by each problem during the past month. A PTSD diagnosis requires a score of ≥ 2 (moderately) for at least one symptom in each of the three clusters plus endorsement of functional impairment associated with these symptoms. For a likely CPTSD diagnosis an additional score of at least ≥ 2 (moderately) is needed for at least one of the symptoms in each of the three DSO clusters. The provisional initial English version of the ITQ demonstrated satisfactory psychometric properties [11, 37, 38]. The Norwegian version was translated at Modum Bad’s Trauma Clinic, and we made some minor adaptions to the final version recently provided to us by the authors of the scale.

General psychological distress is assessed using the Clinical Outcome in Routine Evaluation (CORE-10 [4];), a brief measure of capturing general mental health issues such as anxiety (two items), depression (two items), trauma (one item), physical problems (one item) functioning (three items) and risk to self (one item). It has excellent psychometric properties [4]. Participants are asked to report how often they have experienced the symptoms during the past week on a 5-point Likert scale from 1 (never) to 5 (almost all the time).

Additional trauma-related symptoms are assessed using the Posttraumatic Checklist (PCL-5) [66], a 20-item self-report measure of PTSD based on the criteria from DSM-V. Items are scored on a 5-point scale and range from “not at all” to “extremely”. The scale was found to have adequate psychometric properties [7] and has been translated into Norwegian by the Norwegian Centre for Violence and Traumatic Stress Studies (NKVTS). Moreover, the Brief Dissociative Experience Scale (DE-B), a 9-item short form of the Dissociative Experience Scale-II [12], is included to assess dissociative experiences with regard to memory, identity, awareness and cognition.

Quality of life is assessed using the WHO Five Well-Being Index (WHO-5) [5], one of the most widely used measures of subjective psychological well-being that is also a measure of depression. The scale consists of five simple and non-invasive questions about participants’ well-being experienced during the past 2 weeks, and items are rated on a 6-point scale from 0 (never) to 5 (all the time). A recent review demonstrated that the questionnaire has excellent psychometric properties [65].

Negative and dysfunctional posttraumatic cognitions are assessed using the Posttraumatic Cognition Inventory (PTCI-9) [67], a shortened version of the original 33-item PTCI scale [26]. The scale captures negative cognitions about self, negative cognitions about the world and self-blame. The nine items are rated on a Likert scale ranging from 1 (totally disagree) to 7 (totally agree). Good psychometric properties have been shown for the original and for the newly developed short version [67].

Treatment satisfaction in both conditions is assessed using the Client Satisfaction Questionnaire (CSQ-8 [3];), a shorter version of the original 18-item version [41]. The measure yields a continuous score on a single factor of general satisfaction. This is derived from eight questions about the quality of service, the kind of service, patients’ outcomes and overall satisfaction. The scale is rated on a 4-point response scale and it has been used extensively in research.

Somatic health is assessed in interviews, using a semi-structured interview guide developed for this study; the guide elicits information about somatic illness, sleep problems, diagnoses and treatment in specialized health care. Additionally, height and weight are recorded for calculation of body mass index (BMI). Blood samples will be collected for measurement of changes in the inflammatory markers, interleukin (IL-1, IL-4, IL-6, IL-10), interferon (IFN), tumor necrosis factor (TNF) and transforming growth factor (TGF) from pre-treatment to post-treatment; plasma will be frozen for subsequent analyses of cytokines using the multiplex ELISA technique. Thyrotropin releasing hormone (TRH) and free thyroxine (FT4) will be measured in blood to assess changes in endocrine markers. Register data from three sources will be collected. First, data on use of mental health services 12 months before randomization and at least 12 months after the end of the group intervention will be extracted from the National Patient Register (NPR), which regularly receives data from all health authorities in Norway on treatment episodes in general hospitals, mental health services and substance abuse services. Data will include type of clinical unit, time of admission, length of stay in inpatient units, consultations in outpatient units and mobile teams and diagnoses. Second, data on occupational status will be derived from the nationwide electronic register (NAV/SSB). Extracted data will include welfare or occupational status, number and length of episodes of sick-leave or disability leave. Third, data on use of pharmacological treatment will be collected from hospital records and the national register for pharmacological treatment.

Additionally, participants in two or three of the clusters (both arms; TAU and SST), will be invited to participate in a semi-structured interview to share their experiences of treatment during the last 8 months (since inclusion in the project).

### Fidelity

The manual has yet to be validated and there are no measures of fidelity available to date. To ensure fidelity and adherence to the group intervention, the manual will be actively used in each group session. The manual will also guide the group discussion/s of how to regulate trauma-related affects and interpersonal difficulties relevant to the weekly chapter. Using a checklist, the group leaders rate the presented topics in order to ensure that the core components are delivered in all the courses. Also, when recruiting new group therapists, the new therapists are paired with experienced therapists in accordance with a master-apprentice model.

### Sample size

To the best of our knowledge, there are no established parameters for reliable and/or clinically significant change in the main outcome measure of this study, the QPR-15. We determined the minimal effect size that would be clinically meaningful to be Cohen’s *d* = 0.5; given the costs of implementing SST groups, a smaller effect size would be of little interest to the clinic. Given α = 0.05 and statistical power of 0.80, we calculated that the trial requires a total of 126 participants, 63 in each arm. Accounting for drop-out, which was 20% in the pilot testing of the group intervention, we plan to enrol a total of 160 participants, 80 in each arm. Several of our secondary outcome measures, e.g. the Work and Adjustment Scale (WSAS) are widely used. Three studies utilizing the WSAS comparing new treatments with TAU identified a mean change between the intervention group and TAU from 4.04 [54], 4.5 [55] and 4.6 [21]. These give a mean score of 4.38. The mean standard deviation for pre-treatment and post-treatment scores was 8.5. A power calculation with α = 0.05 and statistical power of 0.80 requires a total sample of 120, which is in line with our first sample size calculation. The estimations are further in line with general recommendations of 75 persons in each arm for studies with two active arms [1].

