The course runs for 20 weeks, and has a fixed rhythm for every session. Each session lasts for 2 h and includes a short break of 15 min. The first hour is a review of the chapter from the previous week, with participants’ reflections and experiences linked to that topic, and feedback on homework and skill training. The second hour is devoted to a new chapter. Based on our previous experiences and feedback from the group participants in the course, participants will be invited to attend a meeting approximately 2 months after completing the course to consolidate their learning and exchange feedback with the other participants and therapists.

Although group sessions are structured, participants are encouraged to share their everyday experiences with coping and handling troublesome episodes related to posttraumatic suffering. The rules and regulations of the group dictate that participants are not permitted to share traumatic or highly upsetting material with the other patients. Instead, participants are encouraged to address any issues that cannot be handled within the group setting with their individual therapist.

Each group has 8–10 participants and the groups are led by two trained therapists from a pool of several professionals who have experience with the treatment manual. Professionals include, to date, two psychomotor physiotherapists, two senior clinical social workers, four psychiatric nurses and three senior clinical psychologists. Some additional clinicians will be recruited as group leaders during the project. New group therapists are paired with experienced therapists in accordance with a master-apprentice model.

The RCT is integrated into routine care; as no serious adverse treatment effects are expected in either condition, there will be no special criteria for discontinuing or modifying allocated interventions. Participants in both conditions will have the opportunity to continue individual treatment after the trial if necessary and appropriate.

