### Statistical methods

The efficacy of the group intervention will be evaluated on an intention-to-treat basis comparing the two arms (SST and TAU). The main efficacy analysis will pertain to the data obtained at post-treatment and 8 months follow up, using *t* tests or mixed models to test for differences in changes in the primary outcome scores from pre-treatment to post-treatment. Baseline characteristics will be tabulated by treatment modality. Per-protocol analyses will also be run.

We will use explorative mediation analyses to investigate whether posttraumatic cognitions influence the outcome measures. We will also consider longitudinal analysis of individual growth curves or analysis of mixed linear models as appropriate.

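### The sample size makes no allowance for clustering within SST therapy groups, and the plan permits a primary t test that would ignore it

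*Protocol article*

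**What the plan says.** The Sample size section takes Cohen's d = "0.5; given the costs of implementing SST groups, a smaller effect size would be of little interest to the clinic". It continues: "Given α = 0.05 and statistical power of 0.80", "we calculated that the trial requires a total of 126 participants, 63 in each arm". Drop-out, "which was 20% in the pilot testing of the group intervention", is the only inflation: "we plan to enrol a total of 160 participants, 80 in each arm". No ICC, design effect or therapy-group size enters this calculation, and none is mentioned in the supporting calculation on the Work and Social Adjustment Scale.

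The Interventions section describes the delivery of SST: "Each group has 8–10 participants and the groups are led by two trained therapists from a pool of several professionals". The course runs for 20 weekly sessions. Both arms keep their existing individual therapist, and the control arm (TAU) has no therapy groups set up by the trial. Under Recruitment procedures and Randomization, patients are gathered in cohorts of about 18–20 and then randomised individually to the two arms.

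For the main efficacy analysis, Statistical methods offers t "tests or mixed models to test for differences in changes in the primary outcome scores from pre-treatment to post-treatment". The choice between the two is not fixed.

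**The concern.** This is an individually randomised trial in which one arm is treated in groups (a partially nested design). Members of an SST group share peers, two leaders and 20 sessions. The Background rests part of the case for SST on processes that arise between group members: normalisation, less shame and corrective relational experience. Leaders also differ in profession and experience. A positive correlation of outcomes within a group is therefore plausible, although the article does not quantify it.

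If that correlation is above zero, the SST mean is less precise than 63 or 64 independent patients would make it. An analysis that ignores the groups then uses too small a standard error and rejects a true null hypothesis more than 5% of the time. An analysis that respects the groups keeps the 5% but has less power than an independent-observations calculation shows. One or the other would affect the single primary comparison, depending on which analysis is run.

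**Working it through.** **Inputs from the article.** d = 0.5, alpha 0.05 (two-sided reproduces the figure), power 0.80, 20% drop-out, 160 enrolled in two arms of 80 (all Sample size); SST groups of 8–10 (Interventions).

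**Assumptions.** ICC 0.02 / 0.05 / 0.10, because none is given. Nine enrolled per group, so 9 × 0.8 = 7.2 analysed per group after drop-out. Standard deviation 1 on the effect-size scale.

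**1. The plan's own figure.** n per arm = 2(1.96 + 0.8416)²/0.5² = 62.8, so 63 per arm and 126 in total. This is exact with a design effect of 1, so no allowance for clustering is hidden in it. Drop-out: 126/0.8 = 157.5, so 158. Conversely 160 × 0.8 = 128, or 64 per arm, which leaves nothing to spare for clustering.

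**2. Clustering in the SST arm only.** Let n be the number analysed per arm, m the analysed group size and k = n/m the number of groups.
- Design effect DE = 1 + (m − 1) × ICC.
- True variance of the arm difference = DE/n + 1/n. The unadjusted variance is 2/n.
- Type I error of the unadjusted test = 2[1 − Φ(1.96 × SE_unadj/SE_true)].
- Power of the unadjusted test = Φ((0.5 − 1.96 × SE_unadj)/SE_true).
- Adjusted power, normal approximation = Φ(0.5/SE_true − 1.96).
- Adjusted power, group-level df: non-central t with Satterthwaite df = (v1 + v2)²/[v1²/(k − 1) + v2²/(n − 1)], where v1 = DE/n and v2 = 1/n.

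Worked example at ICC 0.05, n = 64, m = 7.2:
- DE = 1 + 6.2 × 0.05 = 1.31.
- SE_true = √(2.31/64) = 0.190 and SE_unadj = √(2/64) = 0.177, a ratio of 1.075.
- Unadjusted test: type I error 0.068, power Φ((0.5 − 0.346)/0.190) = 0.79.
- Adjusted test: power Φ(2.63 − 1.96) = 0.75; with k = 8.9 groups the df is 22.9 and power is 0.71.

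| 64 per arm, m = 7.2 | ICC 0.02 | ICC 0.05 | ICC 0.10 |
|---|---|---|---|
| Design effect, SST arm | 1.12 | 1.31 | 1.62 |
| Unadjusted t test: type I error | 0.057 | 0.068 | 0.087 |
| Unadjusted t test: power | 0.80 | 0.79 | 0.78 |
| Adjusted: power, normal | 0.78 | 0.75 | 0.70 |
| Adjusted: power, group-level df | 0.75 | 0.71 | 0.65 |

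Part of the loss in the last row comes from the small number of groups: at ICC 0 the same test has power 0.78, against 0.81 by the normal approximation.

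**3. No loss to follow-up.** With all 80 per arm analysed in groups of 9, adjusted power is 0.86 / 0.82 / 0.76 (normal) or 0.83 / 0.79 / 0.72 (group-level df).

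**4. How much ICC uses up the margin.** Power of 0.80 needs a variance of at most (0.5/2.8016)² = 0.03185. With n = 64 that means DE + 1 ≤ 2.0385, so ICC ≤ 0.0385/6.2 = 0.006. For analysed group sizes from 7.2 to 10 the limit is about 0.004–0.006.

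**5. Check by simulation.** With 8 groups of 8, ICC 0.05 and 20,000 trials per setting, the unadjusted t test had type I error 0.071 and power 0.79; the group-adjusted test had 0.050 and 0.70. The formulae give 0.071, 0.79 and 0.70 for that case.

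**The case against.** **The t test is not fixed.** Statistical methods names mixed models as the alternative. This is a condensed article, and the random-effects structure and degrees of freedom may stand in an analysis plan not shown; their absence here is no fault. This stands, and it limits the criticism of the standard error to the t-test option or to a mixed model without a therapy-group effect. It does not answer the sample size, which is stated here and rests on independence.

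**The size rests on an ICC that the article does not give.** This also stands. At 0.02 the effects are small; only the upper end of the range is serious.

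**The two harms do not add up.** A reader might infer that the primary test is both too liberal and short of power. The table does not support that: the unadjusted test keeps power of 0.78–0.80 and fails on type I error, while the adjusted test holds 5% and loses power.

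**The 64-per-arm case is unfavourable.** Intention to treat and mixed models can use data from people who leave early, and baseline adjustment gains precision. Suppose that the baseline correlation is 0.5 and that d refers to the raw-score standard deviation (neither is stated). The residual variance is then 1 − 0.5² = 0.75, and the variance of the difference with 64 per arm is [0.75 + 6.2 × ICC + 0.75]/64. Power is then 0.88 / 0.84 / 0.78 (normal) or 0.85 / 0.81 / 0.74 (group-level df). A shortfall below 0.80 is therefore possible but not established.

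**Cohorts contain both arms.** Recruitment procedures fills each cohort with SST and TAU patients together. Effects common to a whole cohort largely cancel in the arm difference and do not inflate type I error. The Aims section also calls conventional treatment only mostly individual. This is a reason to allow a cohort term, but it does not remove the correlation that arises inside the SST groups.

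**Conclusion.** The point holds in limited form. The 126 and 160 contain no allowance for clustering within SST groups, and the plan permits a primary t test that would ignore it. For any ICC above zero, that test exceeds its nominal 5%: 0.057–0.087 for ICC 0.02–0.10 with 64 per arm and 7.2 per group. A valid group-adjusted analysis in the same setting has power of 0.70–0.78 (normal) or 0.65–0.75 (group-level df), so 0.80 power at a true 5% level is not reached under those assumptions.

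A reader might take 0.65–0.75 as the trial's power. It is not: the range depends on the assumed ICC, 20% loss and no gain from baseline adjustment. A reader might also conclude that 160 is too few. With groups of 9 and ICC 0.05, 80% power by the normal approximation would need 62.8 × (1 + 1.40)/2 = 75.4, so 76 per arm, 152 evaluable and 152/0.8 = 190 enrolled. That figure rests on the same unverified assumptions, and the article does not show that enrolment must rise.

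**What to change.** In Statistical methods, remove the unadjusted t test as an option for the primary comparison. Specify a mixed model with a random effect for therapy group in the SST arm only, arm-specific residual variances, and Satterthwaite or Kenward–Roger degrees of freedom. A recruitment-cohort term shared by both arms may be added.

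In Sample size, state an assumed ICC range and give the power for the planned 160 over that range, showing the drop-out and baseline-adjustment assumptions, in place of the unqualified 0.80.

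This costs wording only: group membership is known from delivery of the course. No increase in enrolment is proposed, so the change does not restore 0.80 where the ICC is material; it makes the test valid and the stated power accurate. The downside is a less favourable power statement and a slightly wider confidence interval.

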### Randomization

Randomization to the intervention group or TAU will be performed through a web-based system developed and administered by the Unit of Applied Clinical Research, Norwegian University of Science and Technology (NTNU), Trondheim, Norway. Participants will be randomized sequentially, in blocks of variable size (i.e., seven to nine group participants) to ensure even allocation. Participants will be stratified in order to ensure the gender ratio.

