### Recruitment procedures

A total of 160 patients (age ≥ 18 years) will be recruited from the population of patients already receiving treatment in ordinary outpatient clinics. Prospective participants are first informed about the project by their individual therapist. Those who express interest in participating in the study meet with the group therapists together with their individual therapist to receive additional information. Prospective participants then sign an informed consent form and return it by mail or to the reception desk at the clinic. Next, the individual therapist completes a referral questionnaire, which includes basic information including information about previous traumatic incidents based on a standardized checklist, The Stressful Life Events Screening Questionnaire Revised (SLESQ) [30]. The referral documentation also includes information on diagnoses, demographics, current posttraumatic reactions, medication and substance use. In accordance with routine practice at the clinic, the individual therapist performs the diagnostic evaluations based on ICD-10 criteria, and the diagnosis is confirmed in a consensus meeting at the outpatient clinic with participation of at least one specialist in clinical psychology or psychiatry.

All referrals are initially screened for eligibility by a team of group therapists. If the criteria are fulfilled, the participant is added to a waiting list. When sufficient participants are recruited to fill a cluster (approximately 18–20; 9–10 in the intervention group and 9–10 in the TAU group) participants are contacted and invited for initial assessment and randomization. In order to achieve an adequate sample size, therapists will be regularly be reminded of the research project and encouraged to refer eligible participants to it.

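### Allocation is stratified by gender and run in recruitment batches, but the t test allowed as main analysis uses neither factor, which makes it mildly conservative

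*Protocol article*

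**What the plan says.** Three sections of the protocol article bear on this.

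- **Randomization.** Gender is the one named stratification factor: "Participants will be stratified in order to ensure the gender ratio". Blocking is also used: "Participants will be randomized sequentially, in blocks of variable size (i.e., seven to nine group participants) to ensure even allocation".
- **Recruitment procedures.** Eligible patients wait on a list, and baseline assessment and randomisation follow once a course can be filled: "When sufficient participants are recruited to fill a cluster (approximately 18–20; 9–10 in the intervention group and 9–10 in the TAU group". With 160 enrolled, that makes 160/20 = 8 to 160/18 = 8.9, so about eight or nine batches. Registration and trial status puts recruitment between April 2019 and about March 2023.
- **Statistical methods.** The main efficacy analysis, by intention to treat, is to use t "tests or mixed models to test for differences in changes in the primary outcome scores from pre-treatment to post-treatment". No model terms are given for either option. The section adds: "We will also consider longitudinal analysis of individual growth curves or analysis of mixed linear models as appropriate".

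**The concern.** When the arms are balanced on a factor that predicts the outcome, the difference between arm means varies less from one randomisation to another than simple randomisation would imply. An analysis that includes the factor recognises this. A two-sample t test does not, because it leaves the factor's variance in the pooled standard deviation.

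Gender is balanced by design. Batch should be close to balanced, since each batch is divided about equally. Batches are also spread over some four years, and the Interventions section draws group leaders from a pool that will be added to during the project. It is therefore plausible, though not shown, that batch is related to outcome.

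What is at stake is precision: intervals a little wider than the design warrants, and part of the benefit of stratifying given away. Beyond that, one of the two methods named for the main comparison does not correspond to the way patients are allocated.

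**Working it through.** **The plan's own figure.** Sample size gives: "We determined the minimal effect size that would be clinically meaningful to be Cohen’s *d* = 0.5", and "Given α = 0.05 and statistical power of 0.80". Two-sided, n per arm = 2(z₀.₉₇₅ + z₀.₈₀)²/d² = 2(1.960 + 0.842)²/0.25 = 62.8, so 63 per arm and 126 in total, as stated. The t-based solution is 63.8, so 64 per arm. Enrolling 160 with 20% drop-out leaves 160 × 0.8 = 128, or 64 per arm, which is used below.

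**Input not in the documents.** R² is the share of the variance of the analysed QPR change that gender and batch explain together. It is assumed; 5–10% is the working range, with 1% and 20% as outer values.

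**Formulas, with allocation balanced on both factors**

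- True variance of the difference in means: (1 − R²)·2σ²/n. The t test works with 2σ²/n, so its standard error is too large by the factor 1/√(1 − R²).
- True two-sided error rate of the t test: 2[1 − Φ(1.960/√(1 − R²))].
- Power of the t test: Φ((δ − 1.979)/√(1 − R²)), where δ = 0.5·√(64/2) = 2.828 and 1.979 is the critical value on 126 degrees of freedom.
- Power of the adjusted analysis: noncentral t with effect size 0.5/√(1 − R²), which is 0.513 at R² = 0.05 and 0.527 at R² = 0.10.

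| R² (assumed) | SE factor | True α, t test | Power, t test | Power, adjusted |
|---|---|---|---|---|
| 0.01 | 1.005 | 0.049 | 0.803 | 0.805 |
| 0.05 | 1.026 | 0.044 | 0.808 | 0.821 |
| 0.10 | 1.054 | 0.039 | 0.815 | 0.841 |
| 0.20 | 1.118 | 0.028 | 0.829 | 0.881 |

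Worked line at R² = 0.10: √0.90 = 0.9487. The SE factor is 1/0.9487 = 1.054. Power of the t test is Φ(0.849/0.9487) = Φ(0.895) = 0.815.

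The unadjusted power also rises with R², because balance shrinks the true variance whichever test is used. The loss is therefore 0.821 − 0.808 = 1.3 points at R² = 0.05 and 0.841 − 0.815 = 2.6 points at R² = 0.10. Setting the adjusted power against 0.80 would overstate it.

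**Degrees of freedom.** Nine batches cost eight and gender costs one, which takes 126 down to 117. Adjusted power is then 0.8207 and 0.8406, unchanged to two decimals.

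**Simulation.** Eight batches of 16 evaluable patients were simulated, with 25% in the smaller gender stratum and exact balance within batch and gender (10,000 null and 5,000 alternative runs). At R² = 0.065 the type I error was 0.043 for the t test and 0.049 adjusted, with power 0.818 and 0.837. At R² = 0.15 the figures were 0.035 and 0.048, and 0.822 and 0.860. This agrees with the formulas.

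**Effect on the planned size.** By the normal formula, adjustment would lower the required n per arm from 63 to 60 at R² = 0.05 and to 57 at R² = 0.10. It does not raise it.

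**The case against.** The strongest reply is that the article never calls the main analysis unadjusted. It offers mixed models beside the t test, and a mixed model can hold gender and batch. Covariate lists are routinely left to a statistical analysis plan, and this is a condensed article. That much stands: silence about covariates is no fault here, and a reader who infers that the trial is committed to an unadjusted comparison goes beyond the text. What remains is that the article positively names a t test as an acceptable main analysis, and that test has no place for either factor.

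Second, batch is not a declared stratum. Randomization names gender only, and the batch is described as a way of filling a course. This also stands. Balance by batch is implied by the even split, not guaranteed. If it failed, the t test's standard error would be about right and not too large, although adjustment would still gain precision. The mismatch with the stated stratification rests on gender.

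Third, R² has no source in the documents, and because the outcome is change, stable differences in QPR level between genders or batches cancel out. This is fair. R² must refer to change, and it may lie at the low end, where the effect is negligible (1.005 on the standard error at R² = 0.01).

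A reader might also infer that ignoring the design risks false positives or an underpowered trial. For these two factors the direction is the reverse. Correlation among SST patients treated in the same group could make the standard error too small, but that is a different matter, and the stratification text gives it no support.

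**Conclusion.** The point holds in a limited form. The article permits a main analysis that reflects neither the gender stratum nor the recruitment batches. If the t test is the one used, and gender and batch explain 5–10% of the variance of QPR change, intervals are about 2.6–5.4% too wide, the true error rate is about 0.044–0.039, and power is about 0.81–0.815 instead of 0.82–0.84. These figures assume d = 0.5, 64 evaluable per arm, and balance on both factors. Power stays above the planned 0.80 throughout, so 126 evaluable and 160 enrolled are not called into question. If a mixed model containing these terms is used, the problem does not arise. This is a worthwhile, nearly free improvement, not a threat to the validity of the trial.

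**What to change.** Remove the t test as an option for the main comparison. Name one primary analysis: a regression or mixed model of QPR with treatment arm, baseline QPR and the gender stratum. Add recruitment batch as a further covariate, as a fixed effect with eight or nine levels. Apply the same covariates to the continuous secondary outcomes.

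The cost is a clause in the analysis section, settled before outcome data are examined, and seven or eight degrees of freedom for batch plus one for gender, out of about 128 evaluable participants. No change to sample size or allocation is needed. How to handle therapy-group clustering in the SST arm should be decided separately.
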